### Strategies to improve adherence to interventions {11c}

Patients will be informed about the study and the SAA and asked to participate. Since the intervention is implemented once only, no further measures for adherence improvement regarding the intervention are planned. Participants will receive small financial incentives (vouchers) if they complete the study, this also includes all study questionnaires.

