## Interventions

### Explanation for the choice of comparators {6b}

Patients in the control group proceed as usual and only complete questionnaires at the beginning of their waiting period and at the end of the ED visit. Otherwise, they wait without further intervention and receive standard care to ensure that the experimental intervention can be compared to the regular ED procedure. In extraordinary circumstances, patients can be contacted via telephone for up to 72 h to reduce loss-to-follow-up.

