### Criteria for discontinuing or modifying allocated interventions {11b}

Patients will use the SAA with an estimated mean completion time of around 8 min. If patients decide to not finish the assessment, e.g. withdrawal of consent, they will stop using the app and are considered according to the randomized group in the intention to treat analysis but excluded from per protocol analysis.

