#### Other outcomes

Further, we want to assess additional outcomes relating to the SAA. Most of these outcomes are measured in patients of the intervention group exclusively:Certainty in participants’ self-triage decision is measured with a visual analog scale. We consider a 5-point mean difference from baseline to after symptom assessment to be a relevant difference in the intervention group.Trust in the symptom checker is measured using a two-item Likert scale.Trust in the physician is measured using the trust scale of the Cologne Patient Questionnaire (CPQ) [16] in both groups.Usability and usefulness is measured using the System Usability Scale (SUS) [17], the mHealth App Usability Questionnaire (MAUQ) [18], and a self-developed questionnaire for the intervention group only.Diagnostic accuracy is measured by comparing the recommendations of the SAA with diagnoses given in the ED, after discharge and by an independent, external, expert panel blinded to the recommendation given by the app.Triage accuracy is measured by comparing the recommendation of the SAA with the MTS, triage appraisal of the treating physician in the ED, and by an independent, external, expert panel blinded to the recommendation given by the app for cases where discrepancies occurred.

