## Data collection and management

### Plans for assessment and collection of outcomes {18a}

All clinical study data will be registered in a REDCap database (electronic data collection form for clinical studies running on internal servers at Charité – Universitätsmedizin Berlin). The study timeline can be found in Fig. 1. To ensure that ED flow is not compromised through the study, parts of the baseline survey have been flexibilized.Baseline data:Sociodemographical data (e.g., age, sex, level of education)eHealth Literacy (eHEALS) [19]Self-reported health (MEHM) [20]Health anxiety (Item 1 of the German version of the Whiteley-Index WI-d, modified to Likert-scale) [21]Technical affinity (ATI-S) [22]Self-efficacy (ASKU) [23]Anxiety (VAS-A) [15]Patient’s stand-alone triage appraisalSymptom assessment data will be collected through the Ada Health appAn automatically in-app generated report will be downloaded and savedQuestionnaires pre-symptom assessment, after the symptom assessment (Ada), and after the physician encounter will be directly entered into the RedCap database by the participants. To reduce loss-to-follow-up, the survey after the physician encounter can be filled out up to 72h after the contact (e.g. on the ward or via telephone) if extraordinary circumstances prohibit the patient from taking the survey at the intended timepoint. Questionnaires used in the study are:PSQ [12]ZUF-8 [13]VAS-A [15]Trust scale of the CPQ [16]System Usability Scale (SUS) (only for the intervention group) [17]mHealth App Usability Questionnaire (MAUQ) (only for the intervention group) [18]Treating physicians fill out a paper-based survey after the first-patient encounter including the following items:Physician version of the PSQ [12]Triage appraisalRoutine clinical follow-up data after the patient-physician encounter will be collected by a study nurse and directly entered into the RedCap database.ICD-10 codesAssigned triage level (Manchester Triage System, MTS)Discharge typeLength of hospital stayDuration of waiting time

Patients not willing to participate in the trial will be offered to complete an anonymized version of the baseline survey in a paper-based form.

Data collection forms will be made available upon reasonable request by third, academic partners.

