### Plans to promote participant retention and complete follow-up {18b}

The study period for each patient ends after discharge from the ED, not taking clinical record data into account. Therefore, no additional follow-up is necessary, where loss-to-follow-up may occur. Flexibility of assessments shall also improve retention. In addition, there are small financial incentives (vouchers) that will be handed out for completing all surveys up to t3 (Table 1).

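### The protocol states two different voucher conditions: one is harder to meet in the intervention arm, the other stops before the primary PSQ is collected

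*Protocol article*

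**What the plan says.** The voucher condition appears twice in the protocol article.

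- Strategies to improve adherence to interventions {11c}: "Participants will receive small financial incentives (vouchers) if they complete the study, this also includes all study questionnaires". No distinction is made between arms.
- Plans to promote participant retention and complete follow-up {18b}: "small financial incentives (vouchers) that will be handed out for completing all surveys up to t3 (Table 1").

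The questionnaire load differs by arm. Controls, according to Explanation for the choice of comparators {6b}, "only complete questionnaires at the beginning of their waiting period and at the end of the ED visit". Section {18a} adds a survey after the symptom assessment and lists "System Usability Scale (SUS) (only for the intervention group") and "mHealth App Usability Questionnaire (MAUQ) (only for the intervention group"). Other outcomes adds "and a self-developed questionnaire for the intervention group only".

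On patients who do not finish the app, Criteria for discontinuing or modifying allocated interventions {11b} says they are "considered according to the randomized group in the intention to treat analysis" and are left out of the per-protocol analysis. It does not mention the voucher or the later surveys.

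Sample size {14} names two means of keeping attrition down: guidance by study personnel and the financial incentive.

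**The concern.** A retention incentive serves the primary analysis only if it rewards return of the primary outcome and does so on the same terms in both arms. Neither wording achieves this. Under {11c} the same voucher asks for more in the intervention arm. Patients who start the app and stop, a group that can exist only in that arm, appear unable to earn it. Under {18b} the voucher is settled before the PSQ is due.

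If site staff followed {11c}, PSQ return could differ by arm. If those not returning it would have scored differently, the difference in means among responders would be shifted, and recruiting more patients does not remove such a shift. If staff followed {18b}, one of the two stated supports for the 20% loss assumption would not act on the primary outcome at all. If sites read the two sections differently, practice would vary by site.

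**Working it through.** **Step 1. Timing.** In Table 1, t2 follows the symptom assessment, t3 is the physician encounter, and t4 is after the encounter, up to 72 h. The primary outcome is marked at t4 only.

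**Step 2. The two conditions side by side.**

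| | Wording in {11c} | Wording in {18b} |
|---|---|---|
| Surveys needed, control | baseline and end of visit | baseline |
| Surveys needed, intervention | baseline, post-app, end of visit, all app-only forms | baseline, post-app, and any app-only forms given by t3 |
| PSQ (t4) needed for the voucher | yes | no |
| App-stopper meets it, read literally | no: cannot sensibly rate an app not finished | unclear: depends on the t2 survey |

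The post-app survey at t2 falls under both wordings, so the voucher is harder to earn in the intervention arm either way. Only under {11c} does that inequality bear on the PSQ.

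**Step 3. The plan's own figures.** With a standardized difference of 0.3, two-sided alpha 0.05 and power 0.80, the two-sample t-test needs 176 per group, or 352 in total. Then 352 / (1 − 0.20) = 440. Both figures reproduce.

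**Step 4. Power under unequal loss.** With 220 per arm, a 5-point difference and SD 5 / 0.3 = 16.67 (normal approximation):

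- 20% / 20% loss: 176 and 176 responders, power 0.803
- 15% control / 25% intervention: 187 and 165 responders, power 0.802
- 10% / 30%: 198 and 154 responders, power 0.797

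Unequal loss at the same overall 20% costs almost no power. Any harm would come through bias.

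**Step 5. Bias, as an illustration.** In each arm, the responders' mean minus the full-arm mean equals the loss proportion times the gap (responders' mean minus the mean the lost patients would have had). With the same gap in both arms:

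bias = (loss in intervention − loss in control) × gap

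The protocol gives neither loss by arm nor the gap. Both are assumed here, with a gap of 5–10 points.

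| Loss difference | Extra patients lost of 220 | Bias | Share of 5-point target |
|---|---|---|---|
| 2 percentage points | 0.02 × 220 = 4.4 | 0.02 × 5 = 0.1 to 0.02 × 10 = 0.2 | 2–4% |
| 10 percentage points | 0.10 × 220 = 22 | 0.10 × 5 = 0.5 to 0.10 × 10 = 1.0 | 10–20% |

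The first row corresponds to a handful of app-stoppers. The second needs 22 additional losses attributable to the voucher rule, which nothing in the protocol suggests.

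**The case against.** A reader might infer that app-stoppers lose the voucher, that PSQ return will therefore be lower in the intervention arm, and that the primary comparison is biased in favour of the app. The protocol does not support that chain.

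- **Forfeiture is inferred.** No section says an unfinished app run costs the voucher. The requirement in {11c} can be read as the questionnaires given to that participant. The only example of stopping in {11b} is withdrawal of consent, and no voucher rule would recover a PSQ from such a patient.
- **Weaker PSQ return is not shown.** Under {18b} the PSQ is outside the condition in both arms, so there is no between-arm difference in that incentive. Under {11c}, the timing of SUS and MAUQ relative to the PSQ is not given. A patient who has already completed them faces the same remaining task as a control.
- **Loss is attributed elsewhere.** The sample size section puts the 20% down to patient flow in the ED. Staff guidance and completion on the ward or by telephone up to 72 h apply to both arms.
- **The reference to t3 may be a slip** for the survey after the encounter. The two sections would then agree, and only the unequal burden would remain.
- **Operational detail** on vouchers may sit in the full protocol or the patient information.

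Most of this stands against any claim of demonstrated bias. It does not remove the defect in the text. The point is not that detail is missing: the article states the rule twice and differently. If {11c} is followed as written, the condition is unequal between arms. If {18b} is followed as written, the PSQ is not rewarded. A slip in the timepoint label is itself something to correct.

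**Conclusion.** The point holds as an inconsistency in a stated rule, with an avoidable asymmetry between arms. Sections {11c} and {18b} give different voucher conditions, and neither ties the voucher to the primary PSQ on equal terms in both arms.

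Whether this biases the primary comparison, in which direction, and by how much cannot be determined from the protocol. The illustrative range of 0.1–1.0 PSQ points rests on three assumptions: the difference in loss between arms, lost patients scoring 5–10 points lower, and the same gap in both arms. If only a few app-stoppers are affected, the lower end (0.1–0.2 points) applies. A shift toward the app follows only if loss is higher in the intervention arm and lost patients would have scored lower. This is a cheap improvement worth making, and no evidence that the primary result is compromised.

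**What to change.** State one condition, in the same words, in {11c} and {18b}: the voucher is earned in both arms for the surveys common to both, namely baseline and the t4 survey containing the PSQ, whether or not the app or the app-only forms were completed. Correct the timepoint in {18b} to match Table 1. Add to {11b} that patients who stop the app without withdrawing consent are still asked for the t4 survey and can still earn the voucher.

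Costs: SUS, MAUQ and the self-developed form may be slightly less complete (these are other outcomes, not the primary), and a few more vouchers will be given out. Under {25} the change also needs ethics approval, a registry update and notice to study personnel. Recruitment began in April 2022 and this version is dated 28 June 2022, so the rule would change during recruitment. It should take effect in both arms on the same day, with the date recorded. If recruitment has ended, report instead which rule the sites applied, and give PSQ return by arm and among patients who stopped the app.

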### Relevant concomitant care permitted or prohibited during the trial {11d}

No interventions are prohibited. However, the use of other SAA or online health information while waiting is discouraged.

### Provisions for post-trial care {30}

Patient harm from trial participation is not anticipated but all patients are encouraged to re-contact the ED or an ambulatory health care provider in case of deterioration of symptoms as part of standard care. Furthermore, patients are encouraged to contact the principal investigator of the study in case of any study-related questions or problems that might occur.

### Outcomes {12}

#### Primary outcome

The primary outcome is the participants’ satisfaction with the patient-physician-interaction as measured by the the Patient Satisfaction Questionnaire (PSQ) [12]. The intervention is considered successful if we find a mean difference in means of at least 5 points (Scale 0-100) in the intervention group compared to the control group after the first doctor’s contact before discharge, in exceptional cases by telephone within 72h.

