#### Secondary outcomes

The secondary outcomes are as follows:Patients’ satisfaction with the patient-physician interaction is measured using the ZUF-8 [13] (German version of the Client Satisfaction Questionnaire, CSQ-8 [14]). We expect a 1-point mean increase (scale 8–32) between the intervention group and the control group after patients have been treated (at the end of the ED visit before discharge, in exceptional cases by telephone within 72h). In contrast to the PSQ, the CSQ measures satisfaction with the provided health care services.Anxiety is measured using a visual analog scale (VAS-A) [15] at baseline, after the symptom assessment, and at the end of the ED visit. We expect that the potential increase in anxiety after symptom assessment from the baseline value will not be higher than 5 points in the intervention group and that the proportion of patients leaving the ED with higher anxiety values than at baseline will not be higher in the intervention group than in the control group.Physicians’ satisfaction with the patient-physician-interaction as measured by the mean score of the physician version of the Patient Satisfaction Questionnaire (PSQ, physician version) [12]. The intervention regarding this endpoint is considered successful if we find a mean difference in means of at least 5 points (scale 0–100) in the intervention group compared to the control group after patients have been treated.

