### Sample size {14}

In the literature, a mean PSQ-5 score of 81 and a standard deviation of 14–17 can be found [13]. Assuming a clinically relevant difference of 5 points this amounts to a standardized mean difference of around 0.3.

For a fixed sample size design, the sample size required to achieve a power of 1-β = 0.80 for the two-sample *t*-test assuming equal variances at level *α* = 0.05 (two-sided) under these assumptions amounts to 2 × 176 = 352 patients needed (nQuery Advisor®, version 7.0). The drop-out rate is expected to be medium-sized (20%) due to organizational matters regarding patient flow in the ED. However, through guidance by the study personnel and small financial incentives attrition rates are tried to be kept down. Nevertheless, a potential dilution of the treatment effect due to drop-outs is considered. It is assumed that this can be compensated by additional 20 % of patients to be randomized, and therefore the total sample size required for a fixed sample size design amounts to *n* = 440 patients (220 patients per group).

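### The primary success rule (observed difference of at least 5 points) is not the test the trial is powered for; at the assumed true difference of 5 it is met only half of the time

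*Protocol article*

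**What the plan says.** In the Protocol article, Outcomes {12}, Primary outcome, the intervention is "considered successful if we find a mean difference in means of at least 5 points (Scale 0-100") in favour of the intervention group. The condition is on what the trial finds, that is, on the estimate.

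Sample size {14} uses the same number for a different purpose: "Assuming a clinically relevant difference of 5 points this amounts to a standardized mean difference of around 0.3". The literature values given there are "a mean PSQ-5 score of 81 and a standard deviation of 14–17 can be found". The power statement belongs to a significance test: "the sample size required to achieve a power of 1-β = 0.80" for the "two-sample *t*-test assuming equal variances at level *α* = 0.05 (two-sided"), which "amounts to 2 × 176 = 352 patients needed". Allowing for 20% drop-out gives 440 randomised.

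Statistical methods {20a} analyses the primary endpoint with a linear mixed model accounting for site and reports the estimate, 95% confidence interval and p value. It mentions no 5-point threshold.

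Secondary outcomes repeats the rule for the physician version of the questionnaire: "The intervention regarding this endpoint is considered successful if we find a mean difference in means of at least 5 points". No section says how the 5-point rule relates to the significance test.

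**The concern.** The protocol contains two criteria for a positive primary result. One is a test against zero difference, for which the trial is sized. The other is a threshold on the estimate, set exactly at the assumed true effect. An unbiased, symmetric estimate falls below its true value half of the time, so a larger sample cannot raise the chance of meeting the second criterion above 50% when the true difference is 5.

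An estimate between the smallest significant difference and 5 points would be positive by the test and would miss the success criterion. Such a result is quite likely under the plan's own assumptions. With nothing to say which criterion governs, the choice could be made after the result is known. The trial is open-label and its outcome is self-reported, so that choice is better fixed in advance.

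**Working it through.** **Inputs** (Sample size {14} and Primary outcome): assumed true difference 5 points; standardised difference about 0.3, so SD = 5/0.3 = 16.67; literature SD 14 to 17; two-sided alpha 0.05; power 0.80; 176 analysed per group; success threshold 5 points observed.

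**1. The plan's own figure.** The normal approximation gives n = 2 × (1.960 + 0.842)² / 0.3² = 174.4, so 175 per group. The noncentral t solution is 175.4, so 176 per group and 352 in total. With 20% drop-out, 352/0.8 = 440. Power of the t-test at 176 per group is 0.801. The stated figures reproduce.

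**2. Chance of meeting the success rule when the true difference is 5.** With SE = SD × √(2/n),

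P(estimate ≥ 5 | true difference 5) = 1 − Φ((5 − 5)/SE) = 1 − Φ(0) = 0.50.

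SE cancels, so the result holds for every SD and n. A simulation at SD 16.67 and 176 per group gave 0.499.

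**3. Smallest significant difference.** This is t(0.975; 350) × SE, with t = 1.967. At SD 16.67, SE = 16.67 × √(2/176) = 1.777, and 1.967 × 1.777 = 3.49. It lies below 5 throughout the SD range, so requiring significance in addition leaves the 50% unchanged.

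**4. Significant but below the threshold.** Every estimate of 5 or more is significant at 176 per group, so this share is the t-test power minus 0.50.

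**5. True difference needed for an 80% chance of meeting the rule.** 5 + 0.8416 × SE.

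| SD | SE | Smallest significant difference | t-test power at 5 | Significant but below 5 | True difference for 80% chance |
|---|---|---|---|---|---|
| 14 | 1.492 | 2.9 | 0.916 | 0.42 | 6.26 |
| 16.67 | 1.777 | 3.5 | 0.801 | 0.30 | 6.50 |
| 17 | 1.812 | 3.6 | 0.786 | 0.29 | 6.53 |

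**6. Chance of meeting the rule with no true effect.** 1 − Φ(5/SE) is 0.0004 at SD 14 and 0.003 at SD 17. The rule is much stricter than the powered test.

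**7. The reverse conflict** (5 points observed, not significant). This needs t × SD × √(2/n) > 5. At SD 14, 62 per group gives 4.98 and 61 gives 5.02. At SD 16.67 the boundary is 87 per group, and at SD 17 it is 91. So it arises only below about 62 to 91 analysed per group, which is 35% to 52% of the planned 176.

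**The case against.** The best defence is that 5 points is only a benchmark of relevance beside an ordinary superiority test. Sample size {14} calls it clinically relevant, the trial is described as a superiority trial, and Statistical methods {20a} reports estimate, interval and p value without a threshold. Requiring a relevant observed effect is also a legitimate and conservative choice: at the planned size it cannot raise the false-positive rate.

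Part of this stands. A sponsor may choose such a rule, but its power should then be stated. The benchmark reading is weakened by the protocol's own language: the ZUF-8 and the certainty scale are described in terms of expectation or relevance, and only the two PSQ endpoints are given a condition for success. If relevance was all that was meant, the sentence still needs rewording.

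A reader might infer more than the documents support:

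- *That the 80% or the 440 is wrong.* It is not. The 80% is attributed to the t-test, and it is correct for that test.
- *That a significant result below 5 points must be declared a failure.* The text says when the intervention counts as successful, and does not say that nothing else would.
- *That stopping at the end of funding would let a non-significant result count as success.* Trial status allows recruitment to end short of 440, but the conflict needs fewer than about 62 to 91 analysed per group. No section forecasts that, and Recruitment {15} cites around 40,000 patients in the relevant triage categories per 6 months.
- *That the physician PSQ is also underpowered against a claim.* It is a secondary endpoint with no power statement to contradict.

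**Conclusion.** The point holds as a mismatch between the stated success decision and the powered test. If the true difference is 5 points, the success rule is met with probability 0.50, whatever the SD or sample size; this needs only an estimate symmetric around the true value. At 176 analysed per group and SD 16.67, about 30% of trials would be significant with an estimate between about 3.5 and 5 points (29% to 42% for SD 17 to 14). An 80% chance of success under the rule would need a true difference of about 6.3 to 6.5 points. These figures use a two-sample t-test, as the sample size does; site adjustment in the mixed model could change the SE but not the 50%. Any dilution of the effect by drop-out would lower the 50% further. The reverse conflict is secondary and depends on a large recruitment shortfall.

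**What to change.** In Primary outcome, define success as rejection of no difference in the linear mixed model of Statistical methods {20a} at two-sided alpha 0.05, with the difference favouring the app. Keep 5 points as the planning difference and as the benchmark of clinical relevance when reading the estimate and its 95% confidence interval.

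If the sponsor prefers to keep the observed 5-point rule, say in Sample size {14} that its power at a true difference of 5 is 50%, and say how the rule and the significance test combine.

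Align the matching sentence for the physician PSQ in Secondary outcomes, without a power figure, since none is stated for it. Make the change before the primary outcome is analysed.

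The cost is about one sentence in each place. The sample size, randomisation, data collection and model stay as they are. The downside of the preferred option is that success would no longer guarantee an estimate of at least 5 points, so the report should place the estimate and interval against that benchmark.
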